## Abstract

**Background:**

Procrastination, to voluntarily delay an intended course of action despite expecting to be worse-off for the delay, is a persistent behavior pattern that can cause major psychological suffering. Approximately half of the student population and 15%-20% of the adult population are presumed having substantial difficulties due to chronic and recurrent procrastination in their everyday life. However, preconceptions and a lack of knowledge restrict the availability of adequate care. Cognitive behavior therapy (CBT) is often considered treatment of choice, although no clinical trials have previously been carried out.

**Objective:**

The aim of this study will be to test the effects of CBT for procrastination, and to investigate whether it can be delivered via the Internet.

**Methods:**

Participants will be recruited through advertisements in newspapers, other media, and the Internet. Only people residing in Sweden with access to the Internet and suffering from procrastination will be included in the study. A randomized controlled trial with a sample size of 150 participants divided into three groups will be utilized. The treatment group will consist of 50 participants receiving a 10-week CBT intervention with weekly therapist contact. A second treatment group with 50 participants receiving the same treatment, but without therapist contact, will also be employed. The intervention being used for the current study is derived from a self-help book for procrastination written by one of the authors (AR). It includes several CBT techniques commonly used for the treatment of procrastination (eg, behavioral activation, behavioral experiments, stimulus control, and psychoeducation on motivation and different work methods). A control group consisting of 50 participants on a wait-list control will be used to evaluate the effects of the CBT intervention. For ethical reasons, the participants in the control group will gain access to the same intervention following the 10-week treatment period, albeit without therapist contact.

**Results:**

The current study is believed to result in three important findings. First, a CBT intervention is assumed to be beneficial for people suffering from problems caused by procrastination. Second, the degree of therapist contact will have a positive effect on treatment outcome as procrastination can be partially explained as a self-regulatory failure. Third, an Internet based CBT intervention is presumed to be an effective way to administer treatment for procrastination, which is considered highly important, as the availability of adequate care is limited. The current study is therefore believed to render significant knowledge on the treatment of procrastination, as well as providing support for the use of Internet based CBT for difficulties due to delayed tasks and commitments.

**Conclusions:**

To our knowledge, the current study is the first clinical trial to examine the effects of CBT for procrastination, and is assumed to render significant knowledge on the treatment of procrastination, as well as investigating whether it can be delivered via the Internet.

**Trial Registration:**

ClinicalTrials.gov: NCT01842945; http://clinicaltrials.gov/show/NCT01842945 (Archived by WebCite at http://www.webcitation.org/6KSmaXewC).

## Introduction

### Defining Procrastination

Procrastination is defined as “to voluntarily delay an intended course of action despite expecting to be worse-off for the delay” [1]. It involves the postponement of initiating or completing a task or commitment until the last minute, after a predetermined deadline, or indefinitely. Albeit similar to difficulties prioritizing or being self-assertive, procrastination requires an active choice between competing activities, in which one is being avoided in favor of the other [2]. A common explanation for procrastination is based on learning theory and research on motivation and goal setting [3]. According to this perspective, procrastination is the result of an interaction between four variables: (1) expectancy, (2) value, (3) impulsiveness, and (4) time, also known as the procrastination equation [1]. Procrastination is a common behavioral pattern among adolescents and adults, and is presumed to be on the rise because of growing demands on individual responsibility and work flexibility, as well as greater availability of modern information technology [1]. Particularly vulnerable are young people studying at college or university, approximately half of this population suffers from difficulties due to procrastination, compared to 15%-20% in the general public [4]. Procrastination does not only cause problems concerning the task at hand, but has also been related with lower performance in school as well as work, decreased well-being, financial concerns, greater physical and mental illness, and fewer mental health seeking behaviors [5-8]. Both stress and anxiety are common among individuals who procrastinate recurrently, and is correlated with the degree of their difficulties [9,10].

### Procrastination Treatment

Even though procrastination is affiliated with great unrest among those afflicted, research on effective treatment methods is currently lacking. Cognitive behavior therapy (CBT) is often considered the treatment of choice, but since no clinical trials in the field of procrastination have been undertaken to date, its effectiveness is unknown [11]. The assumption that CBT might be beneficial for people suffering from difficulties due to procrastination is therefore primarily based on face validity and singe case studies. However, several of the cognitive and behavioral techniques used with people suffering from procrastination stem from treatment methods that have been proven effective for other psychiatric disorders. Behavioral activation is, for instance, originally developed for depression [12], but is often utilized in situations where a high degree of avoidance is causing great distress and decreased well being [13]. In relation to procrastination, behavioral activation helps the individual change an ongoing behavioral pattern so that tasks and commitments are approached rather than avoided. This usually requires some form of graded exposure considering the fact that procrastination is often reinforced by the unwillingness to experience discomfort [2]. Behavioral experiments can also be used to facilitate a reevaluation of work methods and presumptions regarding one’s own ability to achieve certain goals [14], aspects that are often characterized by either exaggerated optimism or pessimism among people who procrastinate [3]. This is often accompanied by other cognitive therapy techniques that aim to modify rigid and dysfunctional thoughts and assumptions that hinder the individual to behave more flexibly [15]. In addition, recent research findings in cognitive neuroscience and industrial psychology stress the importance of creating an effective work environment (eg, inhibiting the use of multitasking, decreasing the number of distractions, and preventing ego-depletion) [16-18]. In CBT this is generally referred to as stimulus control, and is regarded as beneficial for people who are afflicted by certain stimuli in their environment (eg, managing triggers for anxiety or avoiding situations that can cause problem behaviors such as substance abuse or deliberate self-harm) [19].

The effectiveness of specific CBT techniques for procrastination is however uncertain, thus making it unclear what mediates treatment outcome [11]. Since no clinical trials have yet to be carried out, it is not certain whether cognitive therapy, behavioral therapy, or a combination of both, is best suited for the treatment of procrastination. However, a recent meta-analysis indicates that several interventions related to addressing values and rewards, achieving stimulus control, enhancing goal-setting skills, and the utilization of success-spirals, could be beneficial for people suffering from procrastination [3]. Hence, certain CBT techniques, as well as methods from other disciplines, are assumed to be effective in treating procrastination.

### Trial Objectives and Purpose

The aim of this study is to examine the effects of CBT for procrastination, and to investigate whether it can be delivered via the Internet. The study will be based on a self-help book written by one of the authors (AR) [20], which for the purpose of the current research project has been divided into 10 modules that are to be delivered weekly to the participants. There will be two treatment groups used, one with therapist contact and one without, as well as a wait-list control group. It is assumed that the treatment group with therapist contact will be superior to the treatment group receiving no therapist contact since procrastination can be partially explained as a self-regulatory failure. Both treatment groups are presumed to be superior to the wait-list control.

## Methods

### Participants in the Sample

The current study is a randomized controlled trial (NCT01842945) with a total sample size of 150 participants divided into three groups; treatment with therapist contact (50 participants), treatment without therapist contact (50 participants), and wait-list control (50 participants). For ethical reasons the participants in the control group will gain access to the same intervention following the 10-week treatment period, albeit without therapist contact.

### The Intervention

There will be 10 modules from a self-help book on procrastination administered weekly to the participants via the Internet. These will contain psychoeducation, including information on the mechanisms underlying procrastination, different aspects affecting motivation, the concept of ego-depletion and mental fatigue, as well as a basic rationale of CBT. The modules will also include several techniques commonly used in the treatment of procrastination (eg, behavioral activation, graded exposure, behavioral experiments, identifying and testing rigid beliefs and assumptions, and stimulus control) [3,11,15]. The final module will focus on relapse prevention in order to successfully maintain behavior change [21].

The participants are instructed to study the material and carry out the assignments in each module. This consists of writing down any thoughts and ideas that arise from reading the provided psychoeducation, as well as carrying out different exercises each week (eg, goal-setting, time scheduling, identifying distractions, value clarification, and analyzing behavior patterns. For those participants receiving therapist contact, the completed assignments are retrieved at the end of every week in order to get continuous feedback on their work. This condition is assumed to be superior to those participants that are given each module without therapist contact as procrastination is maintained by difficulties concerning time management and task avoidance [3]. In other words, the presence of an external source of control (ie, a therapist contact) is expected to result in greater treatment outcome, as it will ensure that the participants undertake each module and practice relevant techniques. Similar to homework assignments in traditional face-to-face CBT, which has been found to increase both learning and adherence [22], receiving therapist contact is assumed to improve compliance throughout the treatment period. The feedback from a therapist contact can also be considered a source of positive reinforcement that many participants might lack when working on their day-to-day tasks and commitments [19]. However, even without a therapist contact participants are assumed to gain significant improvement as prior studies of Internet based CBT indicate that also a minimal level of therapist contact can have a positive effect on treatment outcome [23,24].

Internet based CBT has previously been found to be an effective way to administer treatment for several psychiatric conditions [25]. This includes depression [26], social phobia [27], panic disorder [28], generalized anxiety disorder [29], insomnia [30], post-traumatic stress disorder [31], tinnitus [32], and pathological gambling [33] among others. Internet based CBT is considered having several advantages over traditional face-to-face treatment (eg, higher cost-effectiveness, increased accessibility, greater possibility to reach patients in remote locations, and lower attrition rates) [34].

### Control Condition

The participants in the control group will be on a wait-list throughout the 10-week treatment period, and this group is expected to be inferior to the other two treatment groups. For ethical reasons the participants in the control group will gain access to the same intervention following the 10-week treatment period, albeit without therapist contact.

### Sample Size

The current study includes 150 participants randomized into three groups (ie, 50 participants in each group). Since no clinical trials in the field of procrastination have been undertaken, there are no previous effect sizes to take into consideration. However, 50 participants in each group are deemed sufficient to find clinically significant differences.

### Referral and Recruitment

Participants will be recruited through advertisements in newspapers, other media, and on the Internet. Only people residing in Sweden, having Internet access, and suffering from difficulties due to procrastination will be included in the study.

### Inclusion Criteria

Participants will be included in the study if their primary difficulties are caused by chronic and severe procrastination. However, since procrastination is not considered a psychiatric condition there will be no need to utilize diagnostic criteria (ie, Diagnostic and Statistical Manual of Mental Disorders Fourth edition, DSM-IV) [35], or a structured clinical interview (ie, Structured Clinical Interview for DSM-IV) [36]. In order to determine and evaluate the severity of procrastination several primary outcome measures will be used (eg, the Pure Procrastination Scale, PPS; the Irrational Procrastination Scale, IPS; and the Susceptibility to Temptation Scale; STS) [37]. To date, none of the primary outcome measures have clinically established cut-offs. However, greater than 32 points on the IPS have been found to distinguish more severe cases of procrastination (ie, top 25%) [1], and will therefore be used as cut-off for inclusion.

### Exclusion Criteria

In order to be included in the study participants are required to have a Swedish residency, to be at least 18 years of age, and fluent in Swedish, as well as having a computer with Internet access. Participants are not allowed to have an ongoing psychotherapy, and in case of taking psychotropic medication, the dose must have been stabilized for at least three months prior to entering treatment. Psychiatric conditions are not criteria for exclusion as long as procrastination is the primary problem. However, participants with severe depression (> 30 points on the Montgomery Åsberg Depression Rating Scale Self-report version, MADRS-S) [38], suicidal ideation, neuropsychiatric conditions (ie, Attention deficit hyperactivity disorder and Attention deficit disorder) misuse of alcohol or drugs, bipolar disorder, schizophrenia, and psychosis will be excluded from the study.

### Informed Consent

Participation will require a written informed consent.

### Withdrawal

Participation can be withdrawn at any time during the treatment period without specifying a reason behind the decision. In addition, should the condition of a participant deteriorate, supervising clinicians may choose to end the participation prematurely and direct the participant to other health care services.

### Safety Monitoring and Reporting

The current study adheres to the Swedish Personal Data Act [39]. The data being stored will be encrypted, and all participants will receive an auto-generated identification code in order to log on to a secure online interface (eg, 1234abcd), thus ensuring the anonymity of the participants during the analysis of the results. All communication with the participants will take place within the secure online interface that requires an electronic identification (ie, Secure Sockets Layer Certificates). Only reminders to log on to the secure online interface will be sent to the participants’ private email. At the postassessment, and at all subsequent assessment points, questions probing for adverse events will be used [40].

### Primary Outcomes

Primary outcome measures will be self-assessment of procrastination using a Swedish version of the PPS [37], the IPS [37], and the STS [37]. The PPS features 12 items measuring the prevalence of procrastination, and was originally developed to improve the validity of several different procrastination scales [37]. The items used in the PPS have a reliability of .92, and the PPS shows improved convergent validity with other related measures. The IPS features nine items measuring the degree of irrational delay causing procrastination. The items used in the IPS have a reliability of .91, and the IPS correlates together with the PPS at .96, allowing them to be used as parallel forms and share validation efforts [37]. The STS features 11 items measuring the susceptibility to temptation, which can affect the ability to follow through a task or commitment. The items in the STS have a reliability of .89, and demonstrate correlation with both the PPS and the IPS. However, since none of the primary outcome measures contain established cut-offs, clinical assessment will be used to determine treatment outcome. Participants will complete the primary outcome measures before commencing the treatment period, immediately upon completion of the treatment, and at the 12-month follow-up. Participants, including those on wait-list control, will also complete the IPS each week during the treatment period, allowing continuous measurement and increasing the statistical power.

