### Analysis

The study design will allow multiple comparisons-the two treatment groups, with or without therapist contact, will be compared to the wait-list control (separately and together) at posttreatment. In all subsequent analyses, the treatment groups will include those from the control group later randomized to interventions, which will increase the statistical power. The two treatment groups will be contrasted with the control group. Further, the treatment group with therapist contact (group 1) will be contrasted with the group without therapist contact (group 2). At the 12-month follow-up, within-group comparisons will be made with previous results. A number of statistical analyses will be deployed, all of which will be analyzed by the intention-to-treat approach. Treatment outcomes will be examined using mixed-effect models, Bonferroni-correcting for multiple comparisons. This method is deemed preferable to uni- and multivariate repeated measures of variance [46]. Standard missing data analysis (eg, *t* tests, chi-square of severity and sex) will be utilized to determine if unexpected missing data due to participant drop out are random or not.

All outcome measures will be completed directly by the participants via an online interface, minimizing the risk of data loss or data distortion [47,48]. Data will be stored encrypted and in unidentifiable form using an auto-generated identification code.

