### Study Limitations

The current study has some limitations that need to be recognized. First, due to the fact that procrastination is not considered a psychiatric condition there may arise difficulties concerning the evaluation of clinically significant change. In order to assess the effects of the interventions being employed, self-assessments are utilized to determine the severity of procrastination among the participants. However, since none of the primary outcome measures contain clinically established cut-offs, the Reliable Change Index will be used to determine clinical significant change [56]. This might affect the validity and reliability of the results, but is compensated for by the use of secondary outcome measures (eg, MADRS-S, GAD-7 and QOLI), as procrastination often causes great unrest and decreased well being among those afflicted. Second, the use of a Swedish version of the primary outcome measures can also influence the validity of the results, which is why an authorized translator is hired to ensure that no significant loss of meaning is being made during the translation process. Third, another limitation in need of recognition is the involvement of master students in clinical psychology as online therapists. To make up for the students’ lack of training and experience, an experienced licensed clinical psychologist and psychotherapist will supervise all involvement in the study.

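### Treatment outcome is to be judged by clinical assessment in one section and by the Reliable Change Index in another; the first has no described data source and the second does not by itself show clinically significant change

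*Protocol article*

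**What the plan says.** The protocol article gives two rules for judging outcome, each for the same reason.

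- Primary Outcomes: "since none of the primary outcome measures contain established cut-offs, clinical assessment will be used to determine treatment outcome".
- Study Limitations: "since none of the primary outcome measures contain clinically established cut-offs, the Reliable Change Index will be used to determine clinical significant change".

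Three other statements bear on them.

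- **Source of the data.** Primary Outcomes: "Primary outcome measures will be self-assessment of procrastination using a Swedish version of the PPS", together with the IPS and STS. The secondary measures (MADRS-S, GAD-7, QOLI) are also self-assessed. The Analysis section adds: "All outcome measures will be completed directly by the participants via an online interface". For inclusion, "there will be no need to utilize diagnostic criteria" or a structured clinical interview.
- **Group comparison.** Analysis: "Treatment outcomes will be examined using mixed-effect models, Bonferroni-correcting for multiple comparisons". This uses neither of the two rules.
- **Entry level.** Inclusion Criteria: "greater than 32 points on the IPS have been found to distinguish more severe cases of procrastination", described as the top 25%, and this score is the cut-off for entry. The same section says that none of the primary measures has a clinically established cut-off.

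Study Limitations concedes that the lack of cut-offs may weaken the results and offers the secondary scales as compensation.

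**The concern.** A clinical assessment is a judgement; the RCI is arithmetic on questionnaire scores. They can classify the same participant differently, and the article does not say which one governs or that one implements the other.

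Each also has its own difficulty. The clinical assessment has no named assessor, instrument, criterion or data source. The RCI is given a label it does not earn, because it contains no criterion for where the participant ends up.

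At stake is what the trial may say about individuals: how many participants improved to a degree that matters. With two rules in print, the choice between them could be made after the data are seen. With the RCI labelled as planned, a participant who changed by more than measurement error but still procrastinates at about entry level would be counted as clinically improved. The protocol leans on this notion elsewhere too, since Sample Size justifies 50 per group by their sufficiency to find clinically significant differences.

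**Working it through.** The plan states no responder figure, so there is none to reproduce. The check is a comparison of the text, followed by the size of the RCI threshold.

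**1. The two rules side by side**

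| | Primary Outcomes | Study Limitations |
|---|---|---|
| Premise | no established cut-offs | no established cut-offs |
| Rule | clinical assessment | Reliable Change Index |
| What it decides | treatment outcome | clinically significant change |
| Data described for it | none | self-report scores |

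Primary Outcomes, Secondary Outcomes and Analysis describe no clinician-rated measure. Supervising clinicians appear under Withdrawal, Ethics and Study Limitations, but to supervise and to act on deterioration, not to rate outcome.

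**2. What the RCI requires**

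Inputs, from Primary Outcomes: reliability 0.92 (PPS), 0.91 (IPS), 0.89 (STS). No SD is given, so results are in SD units.

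Threshold = 1.96 × √(2 × (1 − reliability))

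- PPS: 1.96 × √(2 × 0.08) = 0.784 SD
- IPS: 1.96 × √(2 × 0.09) = 0.832 SD
- STS: 1.96 × √(2 × 0.11) = 0.919 SD

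Reliability is the only scale-specific input. Nothing in the formula refers to a normal range or to the level at which a participant finishes.

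**3. Where a participant can finish**

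Assume normal IPS scores, with the entry cut-off at the 75th percentile (z = 0.674) because the article calls it the top 25%.

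- The average entrant starts at z = 1.271. After a change exactly at the threshold: 1.271 − 0.832 = 0.439, the 67th percentile.
- An entrant at z = 1.5 ends at 1.5 − 0.832 = 0.668, the 75th percentile, which is about the entry cut-off.
- Any entrant starting above 0.674 + 0.832 = 1.506 can just meet the threshold and still be above the entry cut-off.

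**4. Illustration only: which SD enters the RCI**

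Selecting the top 25% of a normal distribution reduces the SD to 0.49 of the population value. The simulation assumes no true change, a threshold computed with reliability 0.91, and the screening score used as baseline. The share flagged as improved is:

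| Retest correlation | Population SD | Trial SD |
|---|---|---|
| 0.91 | 4% | 24% |
| 0.80 | 17% | 40% |

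If baseline is measured separately from screening, the trial-SD figures fall to about 12% and 17%. If the trial SD is paired with a reliability that matches the restricted sample, the 24% returns to about 4%. The documents do not say which SD or reliability will be used, so these rates describe no choice that the plan makes.

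**The case against.** The strongest reply is that Study Limitations merely says how the clinical assessment will be operationalised, so there is one rule and not two. That reading is possible, but the article does not state it, and if it is right the sentence under Primary Outcomes is still wrong as written, because an RCI computed from self-report is not a clinical assessment.

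A second reply is that the article admits the weakness and compensates with secondary measures. The admission is real. The compensation consists of further self-report scales for depression, anxiety and quality of life. These supply no end-state for procrastination and do not settle which rule applies.

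A third reply is that the main inference rests on mixed models. This stands in full and limits the point to individual-level claims.

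A reader might infer three stronger things, which the documents do not support.

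- *That the RCI will misclassify a quarter or more of unchanged participants.* This requires a published reliability paired with the trial's own restricted SD, which the article does not propose. Details of RCI inputs may properly sit in a full protocol or analysis plan.
- *That unblinded student therapists will rate outcome, mainly in the guided arm.* The article does not say who would assess. The accurate criticism is that the assessment is undefined and has no described data source, not that it is shown to be biased or invalid.
- *That regression to the mean will pass for a treatment effect.* At post-treatment the treated groups are compared with a randomised wait-list selected by the same criterion, so regression is expected equally in all arms. The 12-month comparisons are within-group and lack that protection, but that is a separate matter.

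**Conclusion.** The point holds for individual-level outcome. Two sections draw different rules from one premise. One rule has no described data source. The other shows change beyond measurement error (about 0.78, 0.83 and 0.92 SD for PPS, IPS and STS) and is wrongly described as showing clinically significant change.

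The contradiction and the mislabelling are in the printed text and need no assumption. The thresholds rest only on the stated reliabilities and the usual 1.96 multiplier. The example of finishing near the entry level also assumes normal scores and a cut-off at the 75th percentile. The misclassification rates under range restriction are illustrative and carry no weight in this conclusion.

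This should be corrected, because it changes what the trial may say about responders. It does not threaten the mixed-model comparison between arms.

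**What to change.** 1. Delete the statement under Primary Outcomes that clinical assessment determines outcome, and reconcile that section with Study Limitations into one prespecified rule based on the self-report scores.
2. Report RCI results as reliable improvement and reliable deterioration, not as clinically significant change, and compare the proportions between the randomised arms at post-treatment.
3. Use the term clinically significant only if an end-state criterion is prespecified in addition to reliable change. The share of participants back at or below the entry IPS level could be reported descriptively. It should not be called recovery: the article presents 32 points as a marker of severity and says that no clinical cut-off exists.

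An unrestricted norm sample for the RCI is not made a condition here, since the article gives no norms for the Swedish versions.

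The cost is wording and a small extra analysis, with no new data collection. Fewer participants will be described as clinically improved.
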